### Sample size calculation

The a priori sample size calculation was conducted using G*Power 3.1.9.2 software [44]. It was carried out for the investigation of a between-group difference in the primary endpoint (changes in the HRQoL (PCS and MCS) from baseline to T_3_) in an analysis of covariance model (ANCOVA).

Based on our IEME feasibility randomized clinical trial [16] with four months follow-up of HRQoL, we assume a medium between-group effect size of d = 0.5 on changes in the primary endpoint HRQoL. Level of significance (α) with Bonferroni for multiple comparisons (two primary outcomes) was set at 0.025 and power (1–β) at 0.8. According to Borm et al. 2007 [45], the required sample size for the ANCOVA model was calculated with the formula (1–ρ^2^)**n*. A correlation between participant’s scores at baseline and at T_3_ of ρ = 0.65 was used. The calculation revealed that 90 participants (EG: 45 / CG: 45) would need to be recruited. Based on previous studies that apply similar interventions [16, 22], we have allowed for 18% dropout and plan to recruit 106 participants.

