Recent studies have shown that, in contrast to MCT, HIIT significantly improved aerobic capacity (VO_2peak_), serum levels of MMP-2 and verbal memory [22]. Our feasibility study comparing IEME with PMR has shown a significantly higher level of perceived physical functioning and a significant effect on self-efficacy in performing energy conservation strategies due to the education intervention [16]. In both studies inclusion rates and compliance with the study protocol were high and dropout rates were negligible. HIIT and IEME show effects in different domains of HRQoL. This multidisciplinary study will increase our understanding of detailed exercise training recommendations for PwMS during inpatient rehabilitation and beyond.

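### Recruiting 106 covers about 15% dropout, not the stated 18%, and the basis given for the 18% does not agree with the Discussion

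*Protocol article*

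**What the plan says.** The Sample size calculation section of the protocol article works in two steps.

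- **Required number.** The effect is set by "we assume a medium between-group effect size of d = 0.5", and the alpha and power by "for multiple comparisons (two primary outcomes) was set at 0.025 and power (1–β) at 0.8". The ANCOVA reduction uses a correlation between scores "at baseline and at T_3_ of ρ = 0.65 was used". The result is "The calculation revealed that 90 participants (EG: 45 / CG: 45) would need to be recruited".
- **Dropout.** The allowance is introduced by "Based on previous studies that apply similar interventions [16, 22" and ends with "we have allowed for 18% dropout and plan to recruit 106 participants". The total of 106 is repeated in the Abstract and under Participants and recruitment. The Randomization section gives 53 per arm.

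The Discussion returns to the same two references, 22 for HIIT against MCT and 16 for the IEME feasibility trial. It says of both that "compliance with the study protocol were high and dropout rates were negligible".

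**The concern.** A dropout rate is normally read as the share of recruited participants who are lost before the endpoint. On that reading the required 90, the 18% and the planned 106 cannot all be right, because an 18% loss takes 106 below 90. The stated basis for the 18% is also hard to follow, since the studies it rests on are described elsewhere in the same article as having had negligible dropout.

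At stake is whether the trial still has its required number at six months under its own dropout assumption. A reader also needs to be able to tell where that assumption comes from.

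**Working it through.** **Inputs, all from Sample size calculation:** d = 0.5; alpha 0.025 per primary outcome; power 0.80; rho = 0.65; required N 90 (45 per arm); dropout 18%; planned N 106. The section does not say whether alpha is one- or two-sided. Two-sided is assumed here because only that reproduces 90.

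**Step 1: reproduce the 90.** A two-sample t-test with d = 0.5, two-sided alpha 0.025 and power 0.80 needs 78 per arm, 156 in total. The ANCOVA factor is 1 - 0.65² = 0.5775, and 156 x 0.5775 = 90.09. The stated 90 reproduces. With a one-sided 0.025 the result would be about 74, which does not match.

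**Step 2: reproduce the 106.**

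| Calculation | Result |
|---|---|
| 90 x (1 + 0.18) | 106.2, matches 106 |
| 90 / (1 - 0.18) | 109.8, so 110 (55 per arm) |
| Extra participants as a share of the 90 needed, 16/90 | 17.8% |
| Extra participants as a share of the 106 recruited, 16/106 | 15.1% |
| 106 x (1 - 0.18) | 86.9, about 87 |
| 110 x (1 - 0.18) | 90.2 |

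So 106 agrees with 18% only if the percentage is taken of the 90 needed. Taken of those recruited, 18% leaves 90 - 87 = 3 too few, and covering it would take 110 - 106 = 4 more recruits.

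**Step 3: effect on power.** Adjusting for baseline gives a residual effect of 0.5/√0.5775 = 0.658. The noncentrality is 0.658 x √(N/4), with N - 3 degrees of freedom (two arms, one covariate) and two-sided alpha 0.025. It is assumed that a participant who is lost contributes nothing at T3 and that losses are equal between arms.

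| Analysed N | Noncentrality | Power, t-based | Power, normal approximation |
|---|---|---|---|
| 90 | 3.12 | 79.8% | 81.0% |
| 87 | 3.07 | 78.3% | 79.6% |
| 106 (no loss) | 3.39 | 86.5% | 87.4% |

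The difference between 90 and 87 is 79.8 - 78.3 = 1.5 points (1.4 by the normal approximation). The 0.2 points by which 90 itself misses 80% in the t-based calculation have nothing to do with dropout.

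**Step 4: set the two descriptions of dropout side by side.** Sample size calculation rests the 18% on references 16 and 22. The Discussion discusses those same two references and calls dropout negligible in both. Neither place gives an observed rate, and neither explains why the allowance is higher than negligible.

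**The case against.** **The denominator.** Sixteen extra participants are 17.8% of 90, so 106 is a correct 18% addition to the required number. The protocol prints no inflation formula, so the multiplication by 1.18 is an inference. This stands, and it is why the point is put as a match and not as a known slip. It does not rescue the sentence, which speaks of dropout, and dropout comes out of those recruited.

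**The shortfall is conditional.** If dropout is as low as the Discussion suggests, 106 is more than enough: with no loss, t-based power is about 86.5%. This also stands. The trial falls short of 90 only if losses exceed about 15%.

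**A higher allowance can be defended.** Reference 16 followed participants for four months, whereas the primary endpoint here is at six months and the questionnaires at T2 and T3 are sent and returned by post (Design section). Basing an allowance on earlier studies is also not a claim that they lost 18%. All of this is fair, but the protocol does not give it as the reason. It names the earlier studies and stops there.

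**Stronger readings that the document does not support.** A reader might infer that the whole sample size calculation is inconsistent. It is not: effect size, alpha, power, correlation and the 90 agree with one another, and only the last step does not. A reader might also infer that the Discussion refutes the 18%, or that the allowance should be cut to the earlier rates. The observed rates are not in the article, and at least one of the studies had shorter follow-up, so neither inference is warranted.

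**Conclusion.** The point holds as a small error of statement. With dropout taken as a share of those recruited, 106 covers 15.1% and not 18%. At 18% about 87 remain, 3 short of the required 90, and power for each primary outcome falls from 79.8% to 78.3%. This rests on d = 0.5, rho = 0.65, two-sided alpha 0.025 and lost participants adding no information at T3.

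The loss of 1.5 points arises only if 18% are actually lost. It does not threaten the trial's validity, and a reader should not conclude that the trial is materially underpowered because of its dropout step. The disagreement between Sample size calculation and Discussion is real as wording and calls for an explanation. It does not show that 18% is the wrong allowance.

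**What to change.** In Sample size calculation, choose one of two statements:

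- keep 106 and describe it as allowing for about 15% dropout; or
- keep 18% and state that about 87 participants would then be analysable, with about 78% power per primary outcome.

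Either way, say that the percentage is of those recruited. Then reconcile the section with the Discussion. If the allowance was set above earlier experience because of the six-month postal follow-up, one sentence should say so. If there was another reason, it should be given.

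The cost is one or two sentences and, under the second option, a slightly less favourable power figure. Recruitment, allocation and analysis stay as they are. Four further recruits, to 110, would be needed only if the sponsor wants to keep both 18% and 90 analysable.

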### Statistical analysis

All analyses are conducted according to intention-to-treat. To determine potential effects of between-subjects factor intervention (IEME + HIIT vs. PMR + MCT) and within-subjects factor measurement time-point (T_0_ to T_3_) and their interaction on primary and secondary outcomes, 2 × 4 mixed ANCOVAs will be applied. As covariates, participants’ baseline score of each specific parameter, EDSS score, MS-phenotype, education, smoking status, occupation, time since diagnosis, age and sex will be included into the model. Post hoc Bonferroni corrected pairwise comparisons will be conducted in case of significant main effect of within-subjects factor measurement time-point. Simple effects analyses will be performed to investigate if groups differ at each measurement time-point. As effect size measures, Eta-square and Cohen’s d will be used in ANCOVA and post hoc analyses, respectively. In addition, bivariate correlation analyses will be conducted to determine potential associations between changes in HRQoL (PCS and MCS) and biomarkers/cardiorespiratory fitness/patient-reported outcomes from T_0_ to T_3_.

Statistical analyses will be performed by a statistician blinded to treatment groups, using SPSS 25® (IBM®, Armonk, NY, USA). A result will be considered significant at *p*-value ≤0.05. Because of multiple testing of the primary endpoint, alpha is adjusted in this case and a *p*-value ≤0.025 will be considered significant.

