#### Primary outcome

The primary outcome of this study is the change in HRQoL over six months (T_0_ to T_3_). HRQoL is assessed using the Medical Outcome Study 36-item Short Form Health Survey (SF-36) [32]. This PROM consists of 36 items, divided into eight subscales, summarized in a Physical Component Scale (PCS) and a Mental Component Scale (MCS), with higher scores indicating better HRQoL [33]. HRQoL is assessed at T_0_ and repeated three weeks after baseline (T_1_), four months after baseline (T_2_) and six months after baseline (T_3_).

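### The T0 score is both a response level and a covariate in the same 2 × 4 model. Which tests this distorts depends on the fit, and the T3 group contrast is safe under only one of the two usual fits.

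*Protocol article*

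**What the plan says.** The Statistical analysis section describes one model for primary and secondary outcomes: "within-subjects factor measurement time-point (T_0_ to T_3_) and their interaction on primary and secondary outcomes, 2 × 4 mixed ANCOVAs will be applied". Four levels make T0 a response. The next sentence lists the model's covariates, beginning with the "baseline score of each specific parameter, EDSS score, MS-phenotype, education, smoking status". The Design and Primary outcome sections define baseline as T0, so for the SF-36 summaries the covariate and the first response level are the same number.

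Two sets of follow-up tests are planned on this model. For group differences: "Simple effects analyses will be performed to investigate if groups differ at each measurement time-point". For time: "Post hoc Bonferroni corrected pairwise comparisons will be conducted in case of significant main effect of within-subjects factor measurement time-point". On effect sizes: "As effect size measures, Eta-square and Cohen’s d will be used in ANCOVA and post hoc analyses, respectively". The software is given as SPSS 25, with no procedure named.

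The Sample size calculation section rests on a different and coherent model: an ANCOVA of the between-group difference in change to T3, with ρ = 0.65 between the baseline and T3 scores.

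**The concern.** A variable cannot usefully be both an outcome and a predictor of itself. At T0 the covariate predicts the response perfectly, so that level holds no information about the groups. It nevertheless enters every average over visits, every comparison with T0 and, in some fits, the pooled slope and pooled variance.

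At stake are the validity of the planned time comparisons, the meaning of the group main effect and, depending on the fit, the error rate of the T3 group comparison on which the trial is sized. The article gives this as the model for both primary outcomes (PCS and MCS) and for the secondary outcomes.

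**Working it through.** **Inputs.** From Statistical analysis: response levels T0 to T3, with the baseline score as covariate. From Sample size calculation: d = 0.5, α = 0.025, power 0.8, ρ = 0.65, 45 per arm. Assumptions: two-sided tests; variance 1 at every visit; the same ρ between all visit pairs (the article gives only T0 with T3); the other listed covariates left out.

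**The plan's own figure.** A two-sided t test with these inputs needs 78 per arm, 156 in total. Then 156 × (1 − 0.65²) = 156 × 0.5775 = 90.09, the stated 90. That figure belongs to a baseline-adjusted contrast at T3.

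**Main effect, either fit.** Averaging over four levels gives (0 + d1 + d2 + d3)/4, which is 3/4 of the mean of d1 to d3. A constant 0.50 SD becomes 0.375 SD. The simulated ratio was 0.7500 in both fits. With visit-specific slopes the standard error shrinks by the same factor, so t and p do not change (largest difference in t: 4e-15).

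**Fit A: covariate slope varies by visit (usual GLM repeated measures).**
1. At T0 the slope is 1, the group coefficient 0 and the residual 0. In 500 simulated data sets the T0 group estimate never exceeded 9e-16, nor the residual variance 2e-30. The T0 simple effect is 0/0.
2. For the pooled T3 − T0 comparison the model uses a variance proportional to 1 − ρ² = 0.5775, while the true one is 2(1 − ρ) = 0.70. The SE ratio is √(0.5775/0.70) = √0.825 = 0.908.
3. Type I error at nominal 5% is 2[1 − Φ(1.960 × 0.908)] = 0.075. Six pairs of visits give 0.05/6 = 0.0083, and there it is 2[1 − Φ(2.638 × 0.908)] = 0.017. Simulation (N = 90, 10,000 data sets) gave 0.076 and 0.017. Other values of ρ at nominal 5%: 0.114 (ρ = 0.3), 0.090 (0.5), 0.063 (0.8). Without the T0 covariate, the simulated error at ρ = 0.65 was 0.050.
4. Between-group tests keep their size: the T3 group contrast rejected 0.049 at 0.05 and 0.025 at 0.025, and the group-by-time test 0.049 at 0.05.

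**Fit B: one common slope with a random intercept.**
1. A subject-level covariate with one slope cancels from within-subject differences, so the time comparisons are unaffected. The T0 group contrast is an ordinary number with a standard error.
2. T0 pulls the pooled slope to (1 + 3 × 0.65)/4 = 0.7375, away from 0.65.
3. The model's variance for the T3 contrast is the variance of the four-visit mean given T0, plus 3/4 of the within-subject variance: [3 × 0.5775 + 6 × (0.65 − 0.4225)]/16 + 0.75 × 0.35 = 0.1936 + 0.2625 = 0.4561. The SE is √(0.4561 × 2/45) = 0.142.
4. The true variance is 1 − 2 × 0.7375 × 0.65 + 0.7375² = 0.5852. The SD is √(0.5852 × 2/45) = 0.161.
5. The ratio is 0.142/0.161 ≈ 0.88. Type I error is then 2[1 − Φ(1.960 × 0.88)], about 8% at nominal 5%, and 2[1 − Φ(2.241 × 0.88)], about 4.8% at the primary level of 0.025. Simulation at N = 90 agreed: about 8% at nominal 5%.

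**The case against.** The strongest defence is that the trial's question is between groups at six months, and that the usual repeated-measures GLM answers it correctly despite the duplication: the T3 contrast, the group-by-time test and the main-effect p-value are all unharmed. The planned Eta-square fits that procedure. The time comparisons are post hoc and pooled over arms, and no stated objective rests on them. The T0 simple effect is pre-treatment output that supports no efficacy claim. All of this stands, conditional on visit-specific slopes. But the article does not name the procedure, and under a common slope the harm moves to the T3 group contrast.

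Three stronger readings are tempting and are not supported:
- A reader might infer that the double use of T0 causes the one-quarter shrinkage. It comes from averaging in a pre-treatment level. In a randomized trial any 2 × 4 main effect has it in expectation, with or without the covariate. The article also does not say that it will report this effect in SD units.
- A reader might infer that group comparisons of change from baseline are anti-conservative. Under visit-specific slopes only the time comparisons pooled over arms are.
- A reader might infer that the primary comparison is invalid. That does not follow from the text, since a fit consistent with it leaves the comparison intact.

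An analysis plan may well settle the procedure. That does not cure the wording, because each of the two fits distorts some planned test.

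**Conclusion.** The model as written is mis-specified. With visit-specific slopes the damage is confined to a meaningless T0 test and to pooled visit-versus-T0 comparisons with about 7.5% error at nominal 5% (about 1.7% at 0.0083). With a common slope and random intercept it is the T3 group contrast that suffers, with about 8% error at nominal 5%. The three-quarters factor in the main-effect estimate applies in both fits and is a matter of interpretation.

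The error rates rest on ρ = 0.65, equal variances and equal correlations between visits, with the remaining covariates omitted. The structural points (0/0 at T0 with visit-specific slopes, and the factor 3/4) do not depend on the value of ρ. This is a should-fix: the contradiction is in the text and the repair is easy, but the primary conclusion is threatened under only one of the two fits.

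**What to change.** - Use T1, T2 and T3 as the repeated response (2 × 3), with the T0 score as covariate only.
- Include visit-specific group effects and name the T3 group contrast as the primary test, for PCS and MCS at 0.025 each.
- Drop the simple effect at T0.
- For outcomes measured only at T0 and T1 (cardiorespiratory fitness and blood markers), use a plain ANCOVA of T1 on T0.
- If change since admission is wanted, estimate it in a separate model with T0 as a response level and no T0 covariate.

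The cost is a few sentences of analysis wording. No extra data are needed. The T3 contrast is then the ANCOVA contrast already used in the sample size calculation, so the 90 analysed participants remain as planned.

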## Discussion

This study provides new information on a multimodal therapy approach that combines training and education. For many PwMS, fatigue is the most disabling symptom with a strong impact on HRQoL [5, 46]. Many patients who return home from inpatient rehabilitation (subjectively) report that, after rehabilitation, they are not able to integrate and maintain regular training sessions as part of their daily routine. Being too tired, lack of time and impairment are the most reported barriers for implementing training sessions on a regular basis among PwMS [47, 48]. The energy management program will help the participants to better balance, plan and organize regular sequences of moderate physical activity and exercise in their daily life. It may sound controversial to combine a fatigue management program with high-intensive training that leads to transient exhaustion, but the balance between training and recovery is crucial to build up long-term fitness and thus to have more energy available for an active and satisfying everyday life.

Combining these two therapy approaches may help PwMS to maintain greater physical activity levels after inpatient rehabilitation during everyday life, leading to a sustained increase in HRQoL. Secondary objectives are measured to provide further information on the potential benefits from the endurance exercise modalities and educational interventions. Moreover, they will be captured to identify potential correlations with changes in participants’ HRQoL and to increase knowledge of the impact of a multimodal therapy approach on various aspects relevant to participation. Here, the additional information from after participants return home (T_2_, T_3_) will shed light on the reasons why they are able to apply the energy conservation behaviours and on any barriers or facilitators experienced after they return home.

Recent studies have shown that, in contrast to MCT, HIIT significantly improved aerobic capacity (VO_2peak_), serum levels of MMP-2 and verbal memory [22]. Our feasibility study comparing IEME with PMR has shown a significantly higher level of perceived physical functioning and a significant effect on self-efficacy in performing energy conservation strategies due to the education intervention [16]. In both studies inclusion rates and compliance with the study protocol were high and dropout rates were negligible. HIIT and IEME show effects in different domains of HRQoL. This multidisciplinary study will increase our understanding of detailed exercise training recommendations for PwMS during inpatient rehabilitation and beyond.

## Data Availability

Not applicable.

## Abbreviations

ANCOVA: Analysis of covariance
BCEM-S: Behavior Change in Energy Management-Survey
CG: Control group
CPET: Cardiopulmonary exercise test
EDSS: Expanded Disability Status Scale
EG: Experimental group
ELISA: Enzyme-linked immunosorbent assay
FSMC: Fatigue Scale of Motor and Cognitive function
HADS: Hospital Anxiety and Depression Scale
HIIT: High-intensity interval training
HR_peak_: Peak heart rate
HRQoL: Health-related quality of life
IEME: Inpatient energy management education
IFN-γ: Interferon-gamma
IL-6: Interleukin-6
KA: Kynurenic acid
KYN: Kynurenine
MCS: Mental Component Summary
MMP-2: Matrix metalloproteinase-2
MMSE: Mini-Mental State Examination
MS: Multiple sclerosis
NLR: Neutrophil-to-lymphocyte ratio
OSA: Occupational self-assessment
PCS: Physical Component Summary
PI: Principal investigator
PMR: Progressive muscle relaxation
PROM: Patient-reported outcome measure
PwMS: Persons with multiple sclerosis
rpm: Revolutions per minute
QA: Quinolinic acid
SEPECSA: Self-efficacy of perceived energy conservation strategies assessment
SF-36: Medical Outcome Study 36-item Short Form Health Survey
TRP: Tryptophan
VO_2peak_: Peak oxygen consumption
Watt_peak_: Peak wattage
